### Diabetes in Kerala

Kerala is the most advanced state in India in terms of literacy, health, social uplift and demographic transition.^6^ This has been accompanied by high prevalence of diabetes. A recent report from Kerala suggests that one in five of the Kerala adult population may have diabetes.^7^ The Government of Kerala launched the Aardram Mission in 2017 to transform and gear up the State’s public healthcare system to achieve the sustainable development goals (SDGs) in phases with short-term goals on building infrastructure and quality care services. The overarching objectives of the Aardram Mission included providing equitable, affordable and quality care to citizens from all socioeconomic strata; strengthening the public care system by decentralising healthcare from the secondary and tertiary levels to primary care-led services and initiating preventive medicine to address the impact of non-communicable diseases, especially hypertension and diabetes. Primary care centres have been converted to family health centres (FHCs) with three doctors and four nurses in each FHC assigned to provide individual care plans to the allocated population whose records are tracked through a recently established electronic health records (EHR) called eHealth. The transformation of primary care with a focus on non-communicable diseases provided the backdrop to the implementation of a DR care pathway.

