### Target population

People with diabetes registered in the non-communicable diseases register at 16 FHCs in Thiruvananthapuram district will be invited to be screened for complications of diabetes including screening for DR. As the non-communicable diseases register is likely to show an increase in newly diagnosed diabetes as a result of training the accredited social health activists (ASHAs), in diabetes and DR, we will evaluate the effectiveness of the complex interventions delivered at each of the 16 FHCs for this study. The implementation of the pathway will take into account all patients in the non-communicable diseases register at the start of the cross-sectional study.

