Fidelity	Degree of the DR care pathway implementation. Validation of the DR grading within the telemedicine pathway. Delivery of training and the impact on the DR care pathway.	*Assessment:* Fidelity evaluation in 16 family health centres using a path-process analysis of the screening to identify the common screening pathway across centres. *Data source:* The path-process analysis will be based on detailed time-event logs of 70 patients from the 16 family health centres; a telephone follow-up of referred patients to evaluate uptake of referrals. *Assessment:* Validation of the DR grading will be assessed by the agreement of the DR grade reported by the optometrists at the reading centre in the tertiary centre and those reported by the ophthalmologists in the secondary care centres. *Data sources:* DR grading of referred patients obtained from the reading centre vs secondary care. *Assessment:* Increase in numbers of trained staff per month. *Data sources:* Staff interviews, structured observations and review of facility records. The proportions of doctors trained on laser delivery; data quality on the database; increase in non-communicable diseases registration following start of programme due to training of ASHA workers on diabetes and DR; increase in numbers of patients treated for STDR following training.
Penetration	Increase patient awareness of diabetes and DR and uptake of the DR screening pathway in patients with diabetes.	*Assessment:* Increase uptake of DR screening by patients registered in non-communicable diseases registers. *Data sources:* from non-communicable diseases register and EHR.
Sustainability	Policy makers to prepare policy on up-scale and sustainability plan for DR pathway. Integration of DR pathway in weekly activities in FHCs	*Assessment:* Availability of a policy paper from Government of Kerala on state-wide scale up of the DR care pathway. This will be considered a success of the programme. *Data sources:* Scale up plan for other districts including plan to purchase retinal cameras and acceptance of guidelines and training material for state-wide roll out. *Assessment:* Integration of DR pathway in EHR. *Data source:* EHR records of DR screening as part of non-communicable diseases care pathway.

ASHA, accredited social health activists; DR, diabetic retinopathy; EHR, electronic health records; FHCs, family health centres; STDR, sight-threatening diabetic retinopathy.

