### Sample size

We have chosen the proportion of patients in the non-communicable diseases register with diabetes screened for DR as our primary outcome variable.

Justification of the choice of primary outcome: this variable captures the effectiveness of our intervention as well as the fidelity of implementation. Other facts that informed our choice of the primary outcome is that we expect a short implementation time of 7–9 months during which other outcomes such as number of patients treated may not be a feasible option. Therefore, we have estimated the sample size based on this primary outcome.

Our calculations are complicated by the expected increase in number of people with diabetes in the non-communicable diseases register as public awareness of diabetes and DR increases so the denominator of numbers screened will be the number of people registered in the non-communicable diseases in each FHCs at the start of the cross-sectional study. There is no data on the baseline proportion of patients that attend the tertiary centre for screening. The prevalence of diabetes is between 10% and 16% in Thiruvananthapuram of which 8% are estimated to have DR and 3% to have STDR but about 20% may have to be referred. Assuming a finite population of 40 000 patients with diabetes, a simple random sample of 377 patients will be needed. However, we expect large design effects due to clustering patients within FHCs. There is not enough data to calculate the value of this design effect and therefore we assume it to be 3 to give a final sample size of 1131, which is equivalent to assuming a within-FHCs intracluster correlation coefficient of approximately 0.03 (n=16 FHCs) with negligible residual clustering by the intermediate cluster level of ASHAs, where mean cluster size is smaller.

As described by Becker *et al* in mammography screening,^28^ we expect sources of bias in the implementation programme that will likely influence the sample size calculation. Unscreened DR cases that already exist in the community may contribute to an over-estimation of the effect of screening. We expect lead-time bias because of our short implementation period and so some DR in the community may be missed. A comparison of numbers with DR in FHCs with longer implementation period with those of shorter period may adjust for this bias. We intend to provide a descriptive analysis as well as a temporal comparison using time series analysis.

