One of the strengths of this study is that quantitative data backed by qualitative data will be collected to strengthen our findings and enable generalisation of our findings. Second, we will use robust statistical methods to reduce bias including selection bias and other confounders. Finally, the access to and collaboration with the UK is a key strength of the study, as it facilitates the codevelopment of the interventions from the outset. Active involvement of policy makers engaged in transformation of primary care to screen for and address complications of non-communicable diseases who value research to generate evidence for policy making and who are prepared to learn from, and adapt the DR care pathway based on implementation experience is a unique feature of this study. Findings on the mechanisms and contexts that optimise the implementation of this complex multifaceted intervention using the ERIC taxonomy will be useful to those developing and implementing these programmes in other health systems. The health economic model may highlight the health expenditure required at individual, family and Kerala State level for forecasting and planning health budgets.

Perhaps the most important aspect of the chosen evaluation is that it is built within a simultaneous developing public health strategy on population-based screening of diabetes and hypertension and a recently introduced EHR called eHealth. Conducting research in such an environment is a good example of health policy and systems research.

Despite the limitations, this study holds promise for providing high-quality data and detailed implementation information on a complex intervention in a resources-limited setting. We hope to contribute to the literature on the implementation and effectiveness of DR screening and treatment in the public health sector in LMICs.

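### Two rises listed in the Fidelity row as evidence of training impact, in disease registrations and in patients treated for STDR, cannot be separated from other causes the protocol itself names

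*Protocol article*

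**What the plan says.** The Fidelity row of Table 3 (section Outcomes) includes the indicator "Delivery of training and the impact on the DR care pathway". Its stated assessment is the monthly increase in trained staff. Its data sources are staff interviews, structured observations, facility records, the proportion of doctors trained in laser delivery, data quality and two increases: "increase in non-communicable diseases registration following start of programme due to training of ASHA workers on diabetes and DR" and "increase in numbers of patients treated for STDR following training". The Target population section gives the same explanation for register growth: "the non-communicable diseases register is likely to show an increase in newly diagnosed diabetes as a result of training the accredited social health activists".

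Other sections describe what else is happening:

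- The Discussion says the evaluation is "built within a simultaneous developing public health strategy on population-based screening of diabetes and hypertension and a recently introduced EHR called eHealth".
- The section Diabetes in Kerala says the Government "launched the Aardram Mission in 2017 to transform and gear up the State’s public healthcare system", with a focus on non-communicable disease in primary care.
- The Sample size section refers to an "expected increase in number of people with diabetes in the non-communicable diseases register as public awareness of diabetes and DR increases".
- Description of the standard of care says there is currently no systematic DR screening in the public system. Evidence-based clinical intervention makes screening, referral and treatment of STDR parts of the new pathway.
- Table 1 lists the purchase of retinal lasers (Finance) and a changed clinic timetable in secondary care for referred patients (Infrastructure).

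**The concern.** A simple increase after a start date measures everything that changed after that date. For registrations, the row goes further and states the cause. For treated STDR, it uses a count without a denominator in a programme whose purpose is to send more STDR patients to treatment. Both figures could rise if training had changed nothing, and both would still be entered under the impact of training. What is at stake is the interpretation of one implementation outcome: whether training ASHAs and clinicians altered case-finding and treatment, or whether the rise came from the wider screening strategy, the new record system, the referral flow or the equipment.

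**Working it through.** The protocol attaches no estimate, test or threshold to these two increases, so there is no stated figure to reproduce. The check is a comparison of sections, followed by an illustration.

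**Registrations.** The Fidelity row names one cause, ASHA training. The Discussion names a simultaneous screening strategy for diabetes and hypertension and a new electronic record. The Sample size section names public awareness. Awareness is not a clean rival, because Table 1 has ASHAs trained to raise it on house visits. The screening strategy and the record system are separate from ASHA training. The article gives no registration trend from before the programme and no comparison centres for this count, so the components cannot be separated.

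**Treated STDR.** Write the number of screen-detected patients treated as

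T = S × p × a × t

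where S is the number screened, p the STDR proportion, a the proportion of those cases attending secondary care and t the proportion of attenders treated there. From the Sample size section, p = 0.03. S is not forecast, so 1131 (the calculated sample size) and 40 000 (the assumed diabetic population) serve as a range. The values of a and t are assumptions, with t held at its pre-training level.

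| S | S × 0.03 | T at a = t = 0.5 | T at a = t = 0.8 |
|---|---|---|---|
| 1131 | 33.9 | 33.9 × 0.25 = 8.5 | 33.9 × 0.64 = 21.7 |
| 40 000 | 1200 | 1200 × 0.25 = 300 | 1200 × 0.64 = 768 |

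All of T is added to the treated count without any change in t, provided these patients would not otherwise have been treated in the same period. The count moves with S and a. The ratio T / (S × p × a) equals t and does not depend on how many were screened or attended. That is the reason for the denominator proposed below. The ratio does not remove the effect of newly installed lasers or of a change in case mix.

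**Other planned analyses.** The month-of-entry variable in Statistical analyses belongs to the regression models described there, which concern screening uptake, STDR referral, DR and STDR. The time series comparison in Sample size follows a discussion of bias in DR numbers. Neither is said to apply to registrations or to patients treated.

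**The case against.** The strongest reply is that these are two items at the end of a list of sources. The formal assessment is the number of staff trained, and no success criterion depends on either increase. That stands: a reader might infer that the impact of training is judged from these two counts alone, and the table does not say so.

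Three other stronger readings also fail:

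- A reader might take the treated count to be credited to laser training. The wording is temporal and names no type of training; the link is inferred from the neighbouring laser item.
- A reader might conclude that the rises would contain no training effect. Nurses trained in image capture and newly accredited graders help generate the referrals, and trained ASHAs raise awareness. The point is that the effect cannot be isolated.
- A reader might suppose that the scale-up decision rests on these counts. The Adoption row bases the scale-up plan on clinical and cost-effectiveness data. The primary outcome is also protected from register growth, because its denominator is fixed at the start of the cross-sectional study.

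It is also fair that the screening strategy is described without dates or rates, that the document does not say it enlarged these 16 registers, and that its reach across the state is inferred. The Discussion admits that causal inference is difficult without a concurrent control. That admission is general, however, and it leaves the causal wording of the Fidelity row in place. The condensed form of the article could explain a missing tabulation; it does not explain a cause that is stated in the text.

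**Conclusion.** The point holds in a limited form. Two of several data sources for the impact of training are raw increases that the protocol's own account gives other reasons to expect. Neither can show a training effect, although training may contribute to both. The registration item also states its cause in advance.

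The size cannot be determined from the documents. For treated STDR, 8 to 22 extra patients at 1131 screened shows how the count behaves; it is not an estimate, because it rests on assumed attendance and treatment proportions and on a sample size used in place of a forecast. For registrations no rate is given, so the share due to the concurrent strategy is unknown. The consequence is confined to an implementation outcome. The correction is worth making because it is cheap and because, as written, the row attributes to training what it cannot separate from other causes.

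**What to change.** 1. In the Fidelity row, remove the phrase that assigns the registration rise to ASHA training. Report the rise as occurring alongside the concurrent screening strategy and the awareness work.
2. Report new diabetes registrations per month for each FHC, aligned on its programme-entry date or the date its ASHAs were trained. Where those dates differ between centres, set the counts beside the same calendar months in FHCs not yet started or trained. The article describes staggered entry but does not say that ASHA training dates differ; if they do not, only the comparison by entry date and the monthly trend are available.
3. Replace the count treated for STDR with the proportion of referred STDR patients attending secondary care who are treated there, by month. Show the dates of local laser training and laser installation beside it. Use months before training only where secondary-care records exist.

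The cost is rewording one table row, recording a few dates and making two tabulations. The registers and the data on referred patients are already planned sources. The staggering is not randomised, so the comparisons stay descriptive. Since the standard-of-care section reports no baseline data in primary and secondary care, the pre-training treated proportion may be unobtainable; in that case the monthly series after training should be reported without a before-after claim.

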## Methods

### Design

We chose a type 2 hybrid effectiveness-implementation design to evaluate the effectiveness of the clinical interventions and the implementation strategies.^20–23^ Mixed methods will be used as the method of evaluation. DR care pathway was developed by the Kerala Health Secretary, non-communicable diseases lead, Health and Medical Education service providers, technical and EHR teams, local authorities and the GCRF/UKRI-funded coapplicants from the UK. The DR care pathway will be set-up in a staggered approach with five FHCs initiated in the first 3 months and the remaining 11 centres will be added based on acceptance of all stakeholders and adapting and training phase for 12 months from 15 March 2018. A further 12–15 months will be allocated to recruit consenting patients to a cross-sectional study to gather quantitative data for the effectiveness outcomes. A minimal data set from this study will also be entered into EHR to enable future screening for the consented patients. Qualitative data collection from interviews of staff, patients and focus groups at baseline and end of study and all field notes gathered during the study will be utilised to inform evaluation of the implementation strategy.^20–22^

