	Recruit, designate and train for leadership	A project manager will be recruited to manage the programme under the supervision of the non-communicable diseases lead. The Health Secretary will conduct periodic meetings with the project team to assess performance.
	Obtain formal commitments	A collaborative agreement is in place between Government of Kerala and Moorfields Eye Hospital, London, UK outlining their roles and responsibilities in the implementation of the DR care pathway.
	Prepare patients to be active participants	Community level health workers will prepare patients to be active in their care, to ask questions and specifically to inquire about care guidelines, the evidence behind clinical decisions or about available evidence-supported treatments. Each patient will provide written consent to be screened for DR in this project as well as participate in interviews after verbal consent.
	Inform local opinion leaders	The Health Minister of the Kerala state and members of the local government will be briefed on the project and encouraged to be champions of the project to enable scale up to all family health centres in the state.
Finance	Access new funding	Use GCRF/UKRI funding to purchase smartphone retinal cameras and retinal lasers, develop EHR, train staff at family health centres and secondary care, employ project manager, data entry operators and personnel to conduct interviews, create study database linked to hand-held applications for data entry operators. State and local government funds will be sourced for scale up.
	Incentivisation	ASHAs will be incentivised to accompany participants with diabetes who are referred to secondary care for treatment.
Education	Develop educational materials	Develop DR training modules and retinal image capture modules for family health centres staff Develop laser training material to train ophthalmologists.
	Distribute educational materials	Distribute educational materials (including guidelines, manuals and toolkits) in person, by mail and/or electronically. Multiple training sessions are planned at each family health centres. The camera manufacturers will be invited to provide hands-on training on capturing good quality retinal images. Training on laser surgery will also be provided to the ophthalmologists at secondary care.

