	Change record systems	Change record systems to allow better assessment of implementation or clinical outcomes by having data entry operators interview patients and input full data into EHR within the busy family health centres clinics.
	Change service sites	Change the timetable for clinics in secondary care to allow a patients referred from primary care to access treatment.
	Revise professional roles	The non-communicable diseases lead will be delegated to take on the responsibility of implementing this DR care pathway in Thiruvananthapuram aiming for a Kerala state-wide roll out.
Quality improvement	Develop and implement tools for quality monitoring	Develop, test and introduce into quality-monitoring systems the right input—the appropriate language for the consent form, protocols on DR screening, grading retinal images and measures of processes, patient outcomes and implementation outcomes.
	Develop and organise quality monitoring systems	Develop and organise systems and procedures that monitor clinical processes and/or outcomes for the purpose of quality assurance and improvement.
	Audit and provide feedback	Collect and summarise clinical performance data every month and feedback to family health centres and secondary care staff to monitor, evaluate and modify pathway for acceptability to patients and staff. A continuous monitoring of retinal image quality and gradability, and the referral pathway will be done to cyclically input change into the DR pathway to improve the quality and integration.
	Conduct cyclical small tests of change	Staggered set up of family health centres to allow implementation of changes in a cyclical fashion using small tests of change before taking changes system-wide. Tests of change benefit will be measured continually by increase uptake of training, screening, referral and treatment.
	Use data experts	The EHR team will develop an application for the data entry operators to collect data. The UK collaborators will collaborate in the analysis of the data.
	Use data warehousing techniques	Integrate clinical records from this research project into EHR on an on-going basis.
	Capture and share local knowledge	Capture local knowledge from implementation sites on how staff and doctors make something work in their family health centres and then share it with other centres.
	Obtain and use patients feedback	The participating patients will be asked to provide feedback on the implementation effort.

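### The sustainability indicator of weekly screening at the family health centres is assessed by EHR integration, which the project itself carries out, so weekly delivery is not measured

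*Protocol article*

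**What the plan says.** The Sustainability row of Table 3 (Outcomes) has two indicators. One concerns state policy and a plan for scale-up, and is assessed by whether a Government of Kerala policy paper is available. The other concerns the centres: "Integration of DR pathway in weekly activities in FHCs". The assessment that corresponds to it is "Integration of DR pathway in EHR", and the data source is "EHR records of DR screening as part of non-communicable diseases care pathway".

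Other sections say how DR records get into the EHR:

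- Design: "A minimal data set from this study will also be entered into EHR to enable future screening for the consented patients".
- Table 1, quality improvement (data warehousing): "Integrate clinical records from this research project into EHR on an on-going basis".
- Table 1, infrastructure (record systems): the change consists of "having data entry operators interview patients and input full data into EHR within the busy family health centres clinics".
- Table 1, finance (new funding): the GCRF/UKRI grant is to be used, among other things, to "develop EHR, train staff at family health centres and secondary care, employ project manager, data entry operators and personnel to conduct interviews".
- Table 1, plan (staged scale-up): making sure that the pathway is built into the EHR is listed as a specific action of the implementation strategy.

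**The concern.** The indicator is about recurring behaviour: whether screening has become part of a centre's weekly work. The assessment is about a record system: whether the pathway is in the EHR. The project brings about the second as part of its own strategy, with its own funds. An implementation action is thus used as the measure of an implementation outcome.

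The Abstract says that the pilot is meant to show how the pathway can be scaled up and sustained across Kerala, and that the report will inform adoption by the state. A reader deciding on scale-up would take a favourable sustainability result as evidence that centres had absorbed screening into routine work. The assessment in Table 3 cannot carry that meaning, because it would read the same if screening had depended on project staff and project money.

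**Working it through.** The plan states no figure for this point, so there is nothing to reproduce. The check sets the texts side by side.

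1. **What the indicator needs.** A statement about weekly activity at centres needs a unit (the FHC), a frequency (weeks with screening) and a period.

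2. **What the assessment supplies.** EHR integration, read from EHR screening records. The row attaches no frequency, no per-centre count and no period. The raw material could supply all three, since dated records would show in which weeks a centre screened, but the row does not use them in that way.

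3. **Where the records come from.** Design has study data entered for consented patients. Table 1 has research records integrated on a continuing basis, data entry operators keying data in the clinics, and grant money for EHR development and for those operators. Data collection (Quantitative data) says that nurses or data operators collect the data, so FHC staff also contribute. The article does not say how records from routine care are to be told apart from records created for the study.

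4. **When the records arise.** Design describes a 12-month set-up and training phase and then 12–15 months of recruitment. The sustainability row names no window in relation to the end of project support.

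5. **Does the measure discriminate?** Take two centres:
   - Centre A screens every week with its own nurses and carries on after the project.
   - Centre B screens its consented patients in occasional sessions supported by project operators, and stops when that support ends.

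   Both have the pathway in the EHR, and both have EHR records of DR screening. On the assessment as written they look alike. On a count of weeks with screening they differ during the study, and on a count after support ends they differ completely.

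6. **Does the other sustainability assessment fill the gap?** No. A policy paper and scale-up plan document commitment at state level. They do not observe what centres do. Adoption in the same table also uses a Government policy paper.

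7. **Extent.** Table 3 lists eight implementation outcomes. One of them, Sustainability, is affected, in one of its two indicators, for all 16 FHCs.

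**The case against.** The best case for the plan has five parts.

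- **No pass rule is stated.** A reader might infer that one EHR record per centre satisfies the indicator. The document does not say so: it gives no threshold and no scoring by centre, and a condensed article may leave thresholds and windows to the full protocol. This stands against the stronger reading. It does not remove the point, because the mismatch between indicator and assessment lies in the published table itself.

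- **The label of success belongs elsewhere.** A reader might infer that the plan would call a centre that had stopped screening a programme success. It would not. In Table 3 that label follows the policy paper and is not attached to the EHR assessment.

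- **No weekly frequency can be derived from the sample size.** It is tempting to divide 1131 by 16, which gives about 71 patients per centre, and conclude that a few sessions would do. But 1131 is a minimum sample, not a planned screening volume. The plan invites people with diabetes on the registers of all 16 centres. If the 40 000 assumed under Sample size are those registers, the average is 40 000/16 = 2500 per centre. The number screened per session is not given either.

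- **A drop-off would be visible elsewhere.** Monthly uptake at each centre appears under Acceptability, screening rate per centre and barriers to monthly uptake under Feasibility, and Table 1 has monthly monitoring of patients screened. This limits the harm during the study, since the report would not hide a centre that faded. But none of these is linked to Sustainability, and none is weekly.

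- **A policy commitment is a reasonable proxy at state level.** A pilot in one district cannot observe state-wide continuation. This stands, and there is no need to move the policy paper out of Sustainability.

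**Conclusion.** The point holds in a narrow form. For the indicator on weekly FHC activity, the stated assessment does not measure weekly delivery, and study activity can satisfy it. This is a measure that does not match its indicator, and goes beyond detail left out of a condensed article.

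The documents do not support the further claim that the plan would declare failed centres sustained. The point is about what the measure can show and predicts no particular result.

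The consequence is confined to how one implementation outcome is interpreted. The primary outcome, the sample size and the regression analyses are unaffected. The change is worth making because sustainability is part of the stated aim and the findings are meant to inform a decision on state-wide adoption.

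The conclusion rests on two readings. First, the second assessment in the row belongs to the second indicator, which is the only natural pairing. Second, the wording of the data source, which places the records within the care pathway for non-communicable diseases, is not by itself a rule that excludes study-entered records; the article gives none.

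**What to change.** In the Sustainability row of Table 3, replace the assessment for the weekly-activity indicator with a count that matches it:

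- For each FHC, report the share of weeks with at least one DR screening, from dated EHR entries, over the final months of recruitment.
- If the EHR data remain accessible, report the same share over a window after project support ends. Only this window can speak to continuation.
- Where the EHR records who made the entry, separate entries by FHC staff from those by project-funded operators. The article does not say that such a field exists, analysis uses anonymised extracts, and nurses and operators both collect data, so the split may be incomplete. If it cannot be made, say so.
- If only the in-study window is available, describe the result as weekly integration during the project and not as sustained delivery.
- Keep EHR integration as an implementation action, and keep the policy paper as the state-level sustainability indicator.

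The cost is a rewording of one table row and one extra tabulation of EHR dates. No new patients and no change of design are needed. The downside is small: the sustainability result may look less favourable than a statement that the pathway is in the EHR.
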